## Abstract

**Background:**

Latinos are currently the largest and fastest growing racial/ethnic group in the United States and have the lowest rates nationally of regular sources of primary care. The changing demographics of Latino populations have significant implications for the future health of the nation, particularly with respect to chronic disease. Community-based agencies and clinics alike have a long history of engaging community health workers (CHWs) to provide a broad range of tangible and emotional support strategies for Latinos with chronic diseases. In this paper, we present the protocol for a community intervention designed to evaluate the impact of CHWs in a Community-Clinical Linkage model to address chronic disease through innovative utilization of electronic health records (EHRs) and application of mixed methodologies. Linking Individual Needs to Community and Clinical Services (LINKS) is a 3-year, prospective matched observational study designed to examine the feasibility and impact of CHW-led Community-Clinical Linkages in reducing chronic disease risk and promoting emotional well-being among Latinos living in three U.S.-Mexico border communities.

**Methods:**

The primary aim of LINKS is to create Community-Clinical Linkages between three community health centers and their respective county health departments in southern Arizona. Our primary analysis is to examine the impact of the intervention 6 to 12-months post program entry. We will assess chronic disease risk factors documented in the EHRs of participants versus matched non-participants. By using a prospective matched observational study design with EHRs, we have access to numerous potential comparators to evaluate the intervention effects. Secondary analyses include modeling within-group changes of extended research-collected measures. This approach enhances the overall evaluation with rich data on physical and emotional well-being and health behaviors of study participants that EHR systems do not collect in routine clinical practice.

**Discussion:**

The LINKS intervention has practical implications for the development of Community-Clinical Linkage models. The collaborative and participatory approach in LINKS illustrates an innovative evaluation framework utilizing EHRs and mixed methods research-generated data collection.

**Trial registration:**

This study protocol was retrospectively registered, approved, and made available on Clinicaltrials.gov by NCT03787485 as of December 20, 2018.

**Electronic supplementary material:**

The online version of this article (10.1186/s12889-019-6725-1) contains supplementary material, which is available to authorized users.

## Background

Latinos are currently the largest and fastest growing racial/ethnic group in the United States, constituting 17% of the total population, with the number projected to rise to 28% by 2060 [1]. While a relatively young group, the Latino population is also aging; the median age of Latinos in the U.S. increased from 25 in 2000 to 28 in 2015 [2]. The changing demographics of the Latino population have significant implications for the future health of the nation, particularly with respect to chronic disease. Latinos have the highest lifetime risk for diabetes [3, 4]. Various other cardiovascular disease risk factors, such as obesity, hypercholesterolemia, and hypertension, have also become an increasingly pervasive burden among Latinos in recent years [5].

Chronic disease can have negative impacts on emotional well-being; adults diagnosed with chronic disease are significantly more likely than those without to report lower emotional well-being [6]. Negative emotions, in turn, can reduce one’s ability to self-manage diabetes and engage in modifiable, behavioral risk factors such as a healthy diet and adequate physical activity. Emotional well-being is the perception that life is going well, quality of relationships, positive emotions and resilience, realization of one’s potential, and overall satisfaction with life [7]. Not surprisingly, in caring for patients with chronic disease, primary care providers find themselves increasingly addressing issues such as depression and anxiety that adversely impact disease course. In fact, when chronic disease and emotional health problems are not treated concurrently there is a risk for both conditions to worsen [8]. However, while these co-morbid conditions have received attention in the scientific community public health interventions lag behind and only marginally address emotional health in practice. The result is a system inadequately equipped to address the interconnectivity of these illnesses which subsequently impacts the suffering of individuals and communities.

Community-based agencies and clinics alike have a long history of engaging community health workers (CHWs) to provide support for people with chronic diseases. CHWs are frontline public health workers who belong to or have a trusting relationship with the community they serve [9]. CHWs have been shown to be successful in delivering different types of public health interventions to Latino communities, including health education, preventive health screenings, as well as chronic disease prevention and management interventions [10–18].

### Community-clinical linkages

Historically, CHWs are most recognized for their role in bridging community and clinical services, an early version of the increasingly popular community-clinical linkage (CCL) model [19]. While the CHW approach was fostered in community settings, CCLs are a health systems approach to address disparities that extends the continuum of care from clinical settings to the community [20]. CCLs were designed to improve patient access to community and public health services. The Centers for Disease Control and Prevention (CDC) as well as others have noted the importance of developing CCLs to improve population health and implementation strategies to foster relationships among stakeholders [21–26]. As individuals who serve as a bridge between health care and communities, CHWs provide an ideal connection point for CCLs [27–30]. Further, there is evidence that the social support provided by CHWs can help improve resilience, a key component of emotional well-being, among Latinos with chronic disease. This establishes strong promise for testing CHW-led CCL interventions to improve access to health services and emotional well-being.

### Rationale

As clinics are increasingly integrating the CHW workforce into primary care, it is crucial to ensure that effective and evidence-based CHW community interventions are available to complement clinic efforts. Researchers have sought to delineate the most important and effective roles of CHWs within the clinical setting [31, 32]. Clinic-based CHWs work with patients to support them in disease self-management, navigation of health and social systems, and in health education. Other vital CHW roles such as building community capacity or advocating for individuals and communities, however, may be restricted or not appropriate within the clinical setting [27]. When CHWs have autonomy in their workplace, they are more likely to develop collaborations with peers and other stakeholders [33] and thus are better able to respond to the shifting social determinant of health needs of their clients [34]. With the LINKS study, partners sought to leverage roles and impacts of CHWs in both clinical and community settings.

### Objectives

In this paper, we present the protocol for Linking Individual Needs to Community and Clinical Services (LINKS). A 3-year, prospective matched observational study, LINKS will examine the feasibility and impact of CHW-led CCLs in addressing disparities in chronic disease and emotional well-being among Latinos living in three U.S.-Mexico border communities. We followed reporting guidelines for protocol papers and for intervention descriptions [35, 36]. A list of study sites can be obtained by contacting the corresponding author.

## Methods

### Study team

LINKS was led by researchers from the Arizona Prevention Research Center (AzPRC), funded by the CDC. To better understand the assets and needs of our priority communities, we work closely with a Community Action Board (CAB). Our CAB includes 25 members from stakeholder organizations throughout the region. CAB members provide feedback on intervention design and protocol, translation, and dissemination.

For example, AzPRC researchers developed the emotional well-being questionnaire (see Additional file 1) in consultation with our CAB partners. Selection of the included instruments was an iterative process guided by using reliable and well-validated surveys in the field particularly those tested in the Latino population such as the Quality of Life Short Form [37] and the Center for Epidemiologic Studies Depression Scale [38]. Together we worked with CAB members to balance the interests of our community partners and our research needs.

### Participants

LINKS eligibility criteria included: adults 21 years of age or older who were not pregnant, did not have a serious mental illness, had a chronic disease or a pre-chronic disease including pre-diabetes, glucose intolerance or diabetes, hypertension, and high cholesterol. LINKS took place in Pima, Santa Cruz, and Yuma Counties at county health departments and federally qualified health centers. These three counties are located along the U.S./Mexico border where residents face a disproportionate burden of chronic disease.

### CHWs

CAB research partners hired the community-based CHWs based on their previous work in the field and knowledge about their communities. All four CHWs were bilingual, Latina women with previous CHW or other medical care experience. The research team and the Arizona Community Health Outreach Workers Association (AzCHOW) trained the CHWs in study protocol as well as quantitative and qualitative data collection methods (Table 1), including data entry using Research Electronic Data Capture (REDCap) version 8.5.1 [39]. Training materials are available upon request.

**Table 1 Tab1:** Community Health Working Training Curriculum for Linking Individual Needs to Community and Clinical Services (LINKS)

Training Topic	Community Health Worker Core Consensus Roles [27] Addressed
Introduction to LINKS and Human Subjects Research Training	• Participating in evaluation and research
REDCap Data Entry Training	• Participating in evaluation and research
Cultural Sensitivity and LINKS Participant Recruitment	• Advocating for individuals and communities • Building individual and community capacity • Cultural mediation among individuals, communities and health and social systems • Providing coaching and social support • Providing culturally appropriate health education and information
Emotional Well-being Techniques and Support	• Building individual and community capacity • Providing coaching and social support
Cultural Factors Associated with Social Determinants of Health	• Advocating for individuals and communities • Building individual and community capacity • Care coordination, case management, and system navigation • Cultural mediation among individuals, communities and health and social systems • Providing coaching and social support • Providing culturally appropriate health education and information
Qualitative Methods and Documentation	• Care coordination, case management, and system navigation • Participating in evaluation and research • Providing culturally appropriate health education and information

### LINKS intervention

The three phases of the LINKS intervention, as displayed in Fig. 1, were:Recruitment and referral: Entry into the LINKS program was bi-directional. The clinic-based CHW contacted people in their current patient pool who fit the eligibility criteria as well as identified potential participants in the electronic health records. She referred eligible participants to the community-based CHW via phone call, REDCap message, or in person communication. Alternatively, the community-based CHW recruited participants through word of mouth, clinic waiting rooms, health fairs, or other community settings. Once enrolled, participants were considered “active,” regardless of the extent to which they participated in the community based programming or services. The first participant was enrolled on July 14, 2017. LINKS recruitment was completed on September 30th, 2018.Registration / Assessment: The first interaction between the LINKs community-based CHW and the participants was an in-person, individual meeting. The CHW met with participants for approximately 80 min in the participants’ home, a private office in one of the partnering organizations, or another public location convenient for participants such as the public library in Pima, Santa Cruz, or Yuma Counties. In this meeting, the CHW identified participant priorities and then tailored the LINKS intervention to their needs. She referred them to appropriate programs or services and offered to teach them emotional well-being techniques such as breathing or relaxation exercises. If participants struggled to access the needed service, the CHW accompanied them to their appointment, translated information such as medical insurance letters, or assisted the participants in making phone calls.Follow-up and retention: The LINKS community-based CHW followed-up with each participant individually either face-to-face or over the phone at least once a month for 6 months. If a participant was unavailable, the CHW contacted them the following month. The monthly follow-up was documented in REDCap using the social determinant of health needs assessment form. During these exchanges, the CHW ensured that the participant had accessed any needed resources, referred them to additional services, and offered further emotional well-being technique instruction. If at any point the LINKS participant needed medical assistance, the community-based CHW referred the participant back to the clinic-based CHW. Participants were encouraged to contact the CHW more often if needed both during and after the intervention. Additional follow-ups were also documented in the REDCap database. The community-based CHW repeated the emotional well-being questionnaire at the three and six-month follow ups. As an incentive to complete the intervention, she gave participants $20 and $30 gift cards respectively to thank them for their participation.

**Fig. 1 Fig1:**
[figure not shown]
Outline of Linking Individual Needs to Community and Clinical Services (LINKS) Intervention

We made one major modification to our original protocol. Initially, one of the LINKS inclusion criteria required participants to be patients at one of the partner clinics. The LINKS CHWs urged the university-based team to open recruitment to community members because they found it difficult to turn away people outside the clinic patient pool. On May 18, 2018, we changed our eligibility criteria to include people who were not registered clinic patients. We anticipate recruiting majority clinic patients and that many of the community members may become clinic patients through their connection with the clinic-based CHW.

### Data collection, outcomes and analysis

#### Data collection and management

The research team collected data before, during, and after the six-month LINKS intervention. Using REDCap, the community-based CHWs administered the emotional well-being questionnaire at baseline, three, and 6 months. Monthly, they also conducted the social determinant of health needs assessment and qualitatively documented the issues addressed in their conversations as well as their reflections on the well-being of LINKS participants. The CHWs maintained contact through REDCap messenger, phone, or face-to-face communication. In this way, as participants identified their needs, the CHWs responded with one-on-one support and/or referrals to specific services available through the clinic, county, or other community programs. Clinical partners pulled all laboratory data from the EHR for participants 2 years prior to the intervention, at three and 6 months, as well as after one-year post-intervention (see Table 2).

**Table 2 Tab2:** Linking Individual Needs to Community and Clinical Services (LINKS) Assessment Schedule

Assessment	Measures	Timing
Emotional Well-being Questionnaire	• Behavioral Risk Factor Surveillance System [42] • Short Form 8 Health Survey [43] • Social Support Inventory [44] • State Hope Scale [45] • Center for Epidemiologic Studies Depression Scale [46]	0, 3, 6 months
Social Determinant of Health Needs (CHW follow-up visits)	• Resources needed • Participant-driven utilization • Issues addressed and reflections on participant well being	0–6 months
Clinical Data Collection (Electronic Health Records)	• Glycosylated hemoglobin (HbA1c) • Body mass index (BMI) • Blood pressure • Blood lipid profile	-2 years; 3, 6 months; 1 year

Using an iPad, the community-based CHWs administered the questionnaires and entered participant responses electronically directly into a secure REDCap database. Participant files are stored in numerical order and will be maintained in storage indefinitely after the completion of LINKS. The REDCap data entry screens resembled the paper forms approved by the CAB. We documented modifications to the data written in the database through the REDCap tracking system. To enforce data integrity, each month we completed referential data rules, valid values, range checks, and consistency checks against data already stored in the database. We gave each community-based CHW feedback on their data entry. The privileges associated with each user identification code and password regulated the type of activity that an individual user may undertake. The codebook is available upon request.

#### Primary quantitative outcomes

The primary outcome variables will be extracted from laboratory reports and vitals. They include glycosylated hemoglobin (HbA1c), body mass index (BMI) derived from current weight and height, blood pressure (based on repeated systolic and diastolic reports) and blood lipid profile (e.g. LDL-C, TC, TC/HDL and triglycerides). Data will be abstracted from raw levels when available, with occurrences of chronic disease risk factors identified as consistent with nationwide studies, such as the CDCs’ National Health and Nutrition Examination Survey (NHANES) [40] and the National Diabetes Prevention Program [41].

#### Secondary quantitative outcomes

We will use the emotional well-being survey and social determinants of health needs assessment to measure secondary outcomes including emotional well-being, health behaviors, and CHW-led CCLs. The emotional well-being questionnaire, administered by the community-based CHWs, includes three questions from the Behavioral Risk Factor Surveillance System (BRFSS) [42] regarding self-rated health, social and emotional support, and satisfaction with life. The community-based CHW also rates the participants’ health. Additionally, the emotional well-being questionnaire contains the Short Form 8 Health Survey (SF8) [43], the Social Support Inventory (Enhancing Recovery in Coronary Heart Disease) (SSI) [44], the State Hope Scale (SHS) [45], and the Center for Epidemiologic Studies Depression Scale (CES-D-R 10) [46]. Finally, the emotional well-being questionnaire also includes a single question regarding the amount of physical activity the participant engaged in during the previous week. The community-based CHWs document the resources LINKS participants’ used and needed in the social determinants of health assessment form.

#### Qualitative outcomes

The qualitative data documented by the CHWs in follow-up visits provide narratives of the trajectory of each LINKS participant. The qualitative data offer additional information on the context of the lives of participants and the content of the LINKs intervention. Qualitative outcomes include documentation of social determinant needs that impact health status and the type of social support provided by CHWs to participants.

#### Primary quantitative analysis

Our primary analysis will examine the clinical impact of the LINKS intervention 6 to 12-months post program entry on chronic disease risk factors extracted from the EHR including BMI, HbA1C, blood pressure and lipids. In this prospective matched observational study, the principal analytical strategy is propensity score matching, which will lead to the generation of a natural control group [47, 48] from the health centers existing EHRs. Propensity matching is highly effective in addressing selection bias of known confounders and enables causal inferences when randomization is not possible, feasible or appropriate [49, 50], by creating matched groups with similar covariate distributions [51]. Matched controls will be extracted from the EHR from the participating clinics. Propensity scores will be estimated using logistic regression with the outcome of exposure to the LINKs intervention (or not). Four to one nearest neighbor matching without replacement based on the propensity scores will be used to assemble the analysis sample [52]. Standardized mean differences will be used to assess balance between the groups. The primary analytic models will follow an intention-to-treat approach, with an intervention exposure variable indicating all those who agreed to participate versus their matched comparisons.

Models of the impact of the intervention on these measures will account for the within-person data structure, using (generalized) linear mixed models (GLMM) or generalized estimating equations [53, 54]. Additional analyses will include merged EHR data with the surveys to examine mediation of clinical differences due to prior changes in well-being or behaviors, and will use structural equation modeling. Data are available upon request, based on consultation with community partners.

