#### Secondary quantitative analysis

Within group analysis are planned for the patient reported outcomes. These include repeated responses from the BRFSS [42], SF8 [43], and SSI [44] scales that employed Likert type response formats, with the exception of SSI question 7 (Yes or No: Are you currently married or living with a partner?). Individual items from these three scales will be tabulated and summarized at each administration of the questionnaire. The outcome at each time point for a given subject on a given scale will be the sum of the scores of the items from that scale (excluding SSI question 7). Analyzing the total scale score as opposed to the individual items will hedge against the possibility of a large number of ties between the baseline and follow up questionnaires.

During CES-D-R 10 [46] administration, LINKS participants respond to a list of ways they may have felt or behaved during the past week. A total score for the SHS [45] can be obtained by adding the values of the responses to each item, yielding a score from 6 to 48. The physical activity question asks how many days in the past week LINKS participants have done a total of 30 min or more of physical activity which was enough to raise their breathing rate. Responses from each survey administration will be tabulated. For each of these outcomes, the paired responses between (1) baseline and 3 months follow up and (2) baseline and 6 months follow up will be modelled using GEE or GLMM.

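### The planned mediation analysis has no mediator data in the matched controls, so it cannot show how the intervention-versus-control clinical difference arises

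*Protocol article*

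**What the plan says.** The primary contrast, in the protocol article under Primary quantitative analysis, is "all those who agreed to participate versus their matched comparisons". The comparison group comes from clinic records: "Matched controls will be extracted from the EHR from the participating clinics". The same section then adds a structural equation analysis of "merged EHR data with the surveys to examine mediation of clinical differences due to prior changes in well-being or behaviors". It does not say that this analysis is confined to participants.

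The candidate mediators come from the LINKS survey:

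- Under Data collection and management, "the community-based CHWs administered the emotional well-being questionnaire at baseline, three, and 6 months".
- Under LINKS intervention, the later rounds are part of intervention contact: "The community-based CHW repeated the emotional well-being questionnaire at the three and six-month follow ups".
- The behavior item is also put to participants: "The physical activity question asks how many days in the past week LINKS participants have done a total of 30 min or more" (Secondary quantitative analysis).
- The abstract describes the research-collected measures as including "health behaviors of study participants that EHR systems do not collect in routine clinical practice".
- For these measures the article says "Within group analysis are planned for the patient reported outcomes".

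Table 2 lists the record-based data as HbA1c, BMI, blood pressure and lipids.

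**The concern.** Mediation of an exposure effect has two links: exposure changes the mediator, and the mediator changes the outcome. The first link is a contrast between exposed and unexposed people, so the mediator must be measured in both. Here it is measured only in the exposed. The article accepts this limit for its secondary outcomes, which it analyses within group, but does not carry it over to the mediation sentence.

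Software will not necessarily refuse the model. If control mediator values are treated as missing and handled by full-information likelihood or imputation, an indirect effect may still be returned. It would come from an assumption about how the controls' well-being changed, because the missingness is completely determined by exposure. A reader could then take a reported proportion mediated as evidence that the program improved clinical risk factors by improving well-being, when the data say nothing about that step.

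**Working it through.** **The plan's own figure.** The only sample size stated is for the between-group comparison (Sample size section): 250 LINKS participants, 4:1 controls, difference 0.3 SD, two-sided alpha 0.05/8 = 0.00625, power 90%, 10% loss in the intervention arm.

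- Evaluable participants: n = (1 + 1/4)(z₁ + z₂)²/0.3², with z₁ = 2.734 and z₂ = 1.282. This gives 1.25 × 16.128/0.09 = 224.
- Allowing for loss: 224/0.9 = 248.9, so 249 against 250 stated. The figure is sound.
- It does not cover the mediation analysis, for which no number is given.

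**Mediator data by group.** Participants have the survey at 0, 3 and 6 months. Controls, planned at 4 × 250 = 1,000, have none described.

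**Identification.** Let X be exposure (1 = LINKS, 0 = control), M the mediator change and Y the clinical outcome:

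- M = m₀ + aX + e₁, with variance v_M
- Y = i + c′X + bM + e₂, with variance v_E

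The seven parameters are i, c′, b, m₀, a, v_M and v_E. The indirect effect is ab, and the total effect is c′ + ab. With M seen only when X = 1, the observable moments are:

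- Controls: mean of Y = i + b·m₀; variance of Y = b²v_M + v_E
- Participants: mean of M = m₀ + a; variance of M = v_M; mean of Y = i + c′ + b(m₀ + a); covariance of M and Y = b·v_M; variance of Y = b²v_M + v_E

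The two variances of Y are the same expression, so there are six distinct moments for seven parameters. The numerical Jacobian has rank 6. If M were also observed in controls, the rank would be 7 and the model would be identified.

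The missing piece can be written down. For any shift d, replace m₀ by m₀ + d, a by a − d, i by i − bd, and c′ by c′ + bd. Every moment above is unchanged, but the indirect effect moves from ab to ab − bd.

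**Illustration with assumed values (none is in the article).** Total effect -0.3 SD, mean mediator change in participants +0.4 SD, b = -0.5. Then a = 0.4 − m₀, indirect = -0.5a, direct = -0.3 − indirect, and proportion mediated = indirect/(-0.3).

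| Control mediator change m₀ (unobserved) | a | Indirect | Direct | Proportion mediated |
|---|---|---|---|---|
| -0.2 | 0.6 | -0.3 | 0.0 | 100% |
| 0 | 0.4 | -0.2 | -0.1 | 67% |
| 0.2 | 0.2 | -0.1 | -0.2 | 33% |
| 0.4 | 0.0 | 0.0 | -0.3 | 0% |
| 0.6 | -0.2 | +0.1 | -0.4 | -33% |

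All five rows fit the observable data equally well. The total effect of -0.3 is the same in each, which is why the primary comparison is untouched.

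**The case against.** The strongest reply is that the article never calls these clinical differences between-group. Merging records with surveys naturally leaves only the participants, since nobody else has both, and the article elsewhere analyses survey measures within group. Nor are participants uniform: contact beyond the monthly minimum was logged and resource use was recorded, so a path from service use through well-being to a later clinical value could be fitted among them. Finally, the detail of a structural equation model is commonly left to an analysis plan.

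Much of this stands. The between-group meaning is inferred from placement, not stated, and a within-participant model is estimable. That model would still be observational association among participants, however, and would not explain the difference from controls. An analysis plan can choose among models, but it cannot supply mediator data that the described design does not collect.

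Three stronger readings are tempting, and the documents do not support them:

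- A reader might infer that the survey changes are not really prior, because records are also pulled at 3 and 6 months. The primary clinical window is 6 to 12 months after entry, and a 0-to-3-month change precedes all of it.
- A reader might infer that a well-being pathway is the study's main claim. The stated objective is the feasibility and impact of the linkages, the survey measures are secondary outcomes, and mediation is introduced as an additional analysis.
- A reader might carry the 10% loss allowance over to count the people available for this analysis. That allowance belongs to the between-group calculation, and the article gives no survey completion rate.

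**Conclusion.** The point holds on the reading that the sentence's placement suggests. For mediation of the intervention-versus-control difference, the exposure-to-mediator path, the indirect and direct effects, and the proportion mediated are not identified. Any value reported would rest on an untestable assumption about mediator change in the controls. The table shows that this assumption alone can take the proportion mediated from all of the effect to a negative share. The percentages depend on the assumed inputs; the failure of identification does not.

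The conclusion rests on controls having no survey data, which is how the article describes them. What remains estimable is the total between-group effect and, among participants, the association between survey change and clinical outcome. Reading that association causally needs no unmeasured confounding.

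Severity is moderate: this is an additional analysis, and the primary comparison, the matching and the sample size are unaffected.

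**What to change.** Reword the sentence under Primary quantitative analysis as follows:

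- State that the analysis is restricted to LINKS participants.
- Relate an earlier change in each survey score, for example from 0 to 3 months, to clinical values dated after that survey, adjusting for the baseline clinical value and the baseline score.
- Report the result as association among participants, with no indirect effect or proportion mediated for the intervention.

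The cost is a change of wording and the loss of the mediation claim. Keeping that claim would require the same mediators in a control sample, including a comparable baseline. The article reports that recruitment closed on September 30, 2018, so such a baseline could not now be collected alongside the participants' own.
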